**Participant Recruitment and Enrollment Procedures**

This study will be carried out by Public Health Solutions with the cooperation of one gay-oriented website (e.g., www.manhunt.net), and possibly additional gay-oriented websites (i.e., bigmuscle.com, rentboy.com, and blackgaychat.com) if enrollment figures are not being adequately achieved. All participants in the baseline survey (approximately 10,500) are considered part of the study population and, regardless of whether they are included in the intervention or not, will be included in descriptive analyses. Although one web site is projected as being adequate to meet study goals (N=3,000 randomized into the study), multiple websites may have to be utilized if recruitment is lower than anticipated. A banner ad placed strategically throughout the participating web sites (e.g. chat rooms, exit page) will draw attention to the study. This online recruitment method is considered passive, as opposed to actively recruiting men in chat rooms to take part in the study. Those who click on the recruitment banner (example in Appendix B) will see the first of three consent forms. The first consent form (Appendix C-1) will describe the study in general terms. We will provide our email and phone number contacts here to address further questions about the study. All potential participants will be given the opportunity to exit the site if they do not wish to continue. Following completion of the first informed consent process, participants will be administered the online baseline behavioral survey (Appendix E).

All potential intervention participants who complete the baseline survey, meet study criteria, and provide consent (explained in the second informed consent document) (Appendix C-2) will automatically be randomized into the intervention. After study condition assignments are made, each participant will see one page that describes the assigned condition in more detail (see Appendix D). However, participants in branch 1 will not see anything after the baseline survey other than the post-intervention questions and the resource page that all participants will be shown. Participants in branch 2 will view a text-based standard prevention web-page that contains text and graphics. Participants in branch 3 and 4 will view one of two short videos and those in branch 5 will see both. All participants will then complete a short post-intervention survey (Appendix F) assessing behavioral intentions.

Participants who drop out of the baseline survey, do not answer questions that assess eligibility, or who drop out before randomization will be considered non-responders. Men who are found ineligible for the intervention component of the study will be shown a script such as “Thank you for your time. We appreciate your input in this study. Here are some links to helpful websites about staying healthy.” Participants will then be shown the survey exit page (example in Appendix G), which will provide links to HIV testing, drug and alcohol treatment, mental health hotlines, and information about abstinence, mutual monogamy, and consistent condom use (ABC). For those who are eligible, the second consent form (Appendix C-2) will be presented immediately after the baseline.

All participants will be scheduled for an online follow-up survey 60 days post-intervention, at which time they will receive an email with a hyperlink to the follow-up. A study reminder (Appendix C) will precede the 60-day follow-up survey (Appendix E) and will contain similar information to the second consent. After reading the reminder, participants will choose whether they would like to continue to the survey or not. Regarding intention to treat (ITT), once participants consent and are randomized, they will be kept in their original assignment group and be sent a link to the 60-day follow-up survey even if they do not participate in the intervention activity (i.e., watch video(s) or view standard prevention web page) or answer the post-intervention questions.

**Randomization Procedures**

The goal is to have a randomly assigned study sample of approximately 3,000 participants in five groups balanced within a 5% range. Since chance may not lead to balance, we developed a type of blocking that preserves random assignment while assuring a balanced sample through the duration of the study.

Using the server clock, the decisecond (0,1,2,3,4,5,6,7,8 or 9) when a participant clicks their mouse to go to the “branch” page of the survey is captured.

This “draw” is mapped to the 5 branch groups (a draw of 5-10 is “re-drawn” until a 0-4 comes up), giving us a random draw of 5 numbers. Each half-second, a participant has a 1 in 5 chance of being assigned to any given branch.

When 100 participants have been through the draw, we begin an evaluation procedure to determine the balance among the groups that has been achieved by chance. This process:

- Counts the number assigned to each group
- Determines each group’s percentage of the whole
- Designates each group as:
  - “high,” meaning it contains more than 22.5% of the participants
  - “low,” meaning it contains less than 17.5% of the participants
- Determines if the block (100 records at this point) is “balanced” or “not balanced” within the objective 5% range

If a group (or groups) is “high,” that number is taken out of the “draw” until that group no longer represents more than 22.5% of the whole. This means that during this condition, participants are being randomly assigned to the remaining groups. If one group is “high,” participants have a 1 in 4 chance of being assigned to each of the other groups.

If a group (or groups) is “low,” that number is “emphasized,” meaning an additional number which results in an assignment to that group is added to the “draw” (from the unused 5-9), effectively increasing the chances of assignment to that group from 1 in 5 to 1 in 3. If two groups are emphasized, the chances increase to 1 in 3.5. Again, assignments continue to be made to all groups randomly. (No more than two groups would ever be emphasized at the same time.)

This “nudging” up of low groups and down of high groups continues until the block becomes “balanced” with each group having between 17.5%-22.5% of the whole. Once “balance” is achieved, the next block begins, and the procedure starts again when the next 100 participants have been assigned.

The key point is that random assignment continues through the balancing process. This is preferable to fully preventing assignment to full groups while waiting for the others to “fill up,” which could result in the last group to fill being the only assignment option for a length of time, risking bias and exposing the survey to temporal factors.

In testing, some blocks were balanced at 100 participants. Other blocks took additional participants to balance, resulting in a random range of block sizes. The average block size in tests of a 3,000 participant simulation was 133 records.

**Attrition and Retention Efforts**

Sample selection procedures are designed to produce a sample of approximately 3,000 MSM (600 men per randomized branches 1-5) at the end of the recruitment period. Past formative work, which included piloting an internet-based intervention with a 90-day follow-up survey, showed an attrition rate of 45%, with slightly less than 500 of the 1,000 men who provided emails completing the follow-up survey. Given the shorter follow-up period (60 day follow-up) in this research study, we expect a lower overall attrition rate and a differential attrition rate by branch. We estimate that control branch 1 and standard text-based prevention web page branch 2 will yield an approximate attrition of 240 (40%) participants, and video treatment branches 3-5 will yield an approximate attrition of 180 (30%) participants. We are expecting higher attrition for branches 1 and 2 since there is no video component, which is more engaging.

We will make efforts to minimize study attrition by sending up to 4 reminder emails (Appendix C-3) to participants during the course of the follow-up period. For participants who do not respond to the follow-up email, we will wait approximately 1 week before sending a first reminder email, approximately another week before sending the second reminder, and approximately one more week before sending the final reminder email. In our previous work, virtually no additional responses were obtained after 3 reminders.

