**Information Management and Analysis Software**

The Web Development and Programming staff will program the surveys and electronic consent forms, and program computerized randomization for consenting intervention participants. Completed baseline and follow-up surveys will be downloaded into a SQL database, and then cleaned for missing data and incomplete cases. Statistical Software for the Social Sciences (SPSS) Version 14.0 and SAS 9.1 will be used for data cleaning and analysis.

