***Follow-up*: Validation of the Online Video as an Intervention**

Of the 1,002 men who completed the survey and provided emails, 3 months later, 908 emails were still working. Emails linking to the follow-up survey were sent 1/17, 1/23 and 2/1/06 to 908/1,002. No incentives were provided. Preliminary analysis compared disclosure of HIV status to sexual partners and HIV testing, before and in the 3 months after watching the video, by McNemar and Pearson Chi-square tests. Three months after watching the video, 496 of 908 men (55%) with working emails completed the follow-up survey. Men completing follow-up and those who did not were similar by race/ethnicity (14% Hispanic, 72% white, 6% black, 2% Asian, 6% mixed/other), age (mean 38) and prevalence of unprotected anal intercourse with a new/casual partner (36%), but were significantly more likely to have a college degree (55% vs. 47%, p=.01). Statistically significant behavior changes were found. Men were 3 times more likely to ask their partner’s HIV status (OR=3.0, p<.001) and two times more likely to disclose their own(OR=2.2, p<.001) at follow-up compared to baseline. The 318 HIV-negative men participating in the evaluation were also three times more likely to report HIV testing during follow-up (42%) than in the 3 months before baseline (20%) (OR=2.8, p<.001). These findings strongly suggest that online interventions designed to engage critical thinking are an efficient and effective way to influence behavior change in large numbers of at-risk MSM.

We examined the prevalence and stability of drug and alcohol use between baseline and follow-up. At baseline, 7% reported methamphetamine use in their last sexual encounter. At follow-up, 5% reported methamphetamine in their last encounter. Out of the methamphetamine users at baseline, 39% followed up and were significantly LESS likely than non-users to follow-up (OR 0.6, p<.05). Contrary to methamphetamine use, other drug use (i.e., poppers, marijuana, MDMA, GHB, cocaine) as well as alcohol use, reported between baseline and follow-up remained stable. Specifically, there were no significant differences in the proportions of men reporting drug or alcohol use at baseline compared to follow-up. Drug use at baseline and follow-up was 24% and 32%; alcohol use was 27% at both baseline and follow-up.

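### The protocol predicts branch-driven dropout along its primary contrast, but every named analysis relies on men who return the 60-day survey and none deals with those who do not

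*Protocol*

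**What the plan says.** **Expected dropout (Protocol, Attrition and Retention Efforts).** "We estimate that control branch 1 and standard text-based prevention web page branch 2 will yield an approximate attrition of 240 (40%) participants", while "video treatment branches 3-5 will yield an approximate attrition of 180 (30%) participants". The reason given is the assignment itself: "We are expecting higher attrition for branches 1 and 2 since there is no video component, which is more engaging".

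**Primary contrast (Specific Aims and Hypotheses).** Aim 3 compares branches 3, 4 and 5 with branches 1 and 2 on change from baseline to 60 days in disclosure, testing and condom use.

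**Intention to treat (Participant Recruitment and Enrollment Procedures).** "Regarding intention to treat (ITT), once participants consent and are randomized, they will be kept in their original assignment group", and they are sent the follow-up link even if they skip the intervention or the post-intervention questions. How a man without a 60-day survey enters the analysis is not stated.

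**Analyses (Sampling, Sample Size, and Statistical Power; Data Handling and Analysis).** Chi-square tests between branches, McNemar's test within branches, logistic regression with the pretest value and treatment, and linear regression with interaction terms. Power is based on the men retained.

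**Incomplete records (Information Management and Analysis Software).** Downloaded surveys are "then cleaned for missing data and incomplete cases".

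**Pilot (Appendix A, Follow-up).** "Out of the methamphetamine users at baseline, 39% followed up and were significantly LESS likely than non-users to follow-up", with an odds ratio of 0.6. Responders more often had a college degree (55% vs 47%). Responders and non-responders were similar on age, race/ethnicity and unprotected anal intercourse with a new or casual partner (36%).

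**The concern.** Randomisation makes the branches comparable at entry. It does not make the men who answer at 60 days comparable, and the protocol itself expects the branch to influence who answers. The expected gap falls exactly between the two sides of the primary hypothesis.

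The other safeguards do not reach this problem:

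- The baseline balance check compares the randomised groups, not the responders.
- The planned comparison of completers with non-completers concerns the intervention activities, not the 60-day survey.
- Neither the section on bias nor the limitations mentions attrition.

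At stake is whether a small advantage for the videos could be told apart from the retention advantage that the protocol expects them to have.

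**Working it through.** **1. The plan's own figures.**
- Dropout: 0.40 × 600 = 240 and 0.30 × 600 = 180. Both reproduce. Retained: 360 and 420 per branch.
- Primary contrast among responders: 2 × 360 = 720 vs 3 × 420 = 1,260.
- Total retained: 720 + 1,260 = 1,980 (66.0% of 3,000). The power section uses 70% and 2,111, which is 131 more, so the differential attrition was not carried into it.

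**2. Which analyses need the 60-day survey.** The primary outcomes are changes from baseline to 60 days. McNemar's test needs both surveys from the same man. The regressions need a follow-up outcome. With no other step named, a man without that survey contributes to none of them.

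**3. Is non-response selective in the pilot?** Inputs from Appendix A: 1,002 men with valid emails, 496 responders, 7% methamphetamine use at baseline (assumed to apply to the 1,002), 39% of users responding.
- Users: 0.07 × 1,002 = 70.1, of whom 0.39 × 70.1 = 27.4 respond.
- Non-users: (496 − 27.4)/(1,002 − 70.1) = 50.3% respond.
- Odds ratio: (0.39/0.61)/(0.503/0.497) = 0.63, in line with the reported 0.6. On the 908 working emails the same steps give 0.51, so the 1,002 base fits better.
- Users' share of responders: 27.4/496 = 5.5%, against 7% at baseline.

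**4. Bias with no true effect.** Assumptions: true rate 20% to 42% (the pilot's HIV testing rates, used as a range); follow-up 60% vs 70%; odds ratio between having the outcome and responding of 1, 0.6 or 1/0.6 = 1.67. The 0.6 is borrowed from the methamphetamine association.

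The responder rate is P(outcome) × P(respond given outcome) / P(respond). At a true rate of 20%:
- Odds ratio 0.6, 60% follow-up: men with the outcome respond at 50.0%, others at 62.5%. Responder rate = 0.20 × 0.500/0.60 = 16.7%.
- Odds ratio 0.6, 70% follow-up: 61.0% and 72.3%. Responder rate = 0.20 × 0.610/0.70 = 17.4%.
- Odds ratio 1.67, 70% follow-up: 78.0% and 68.0%. Responder rate = 0.20 × 0.780/0.70 = 22.3%.

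Equal mild selection therefore gives a spurious 0.8 points (17.4% against 16.7%, before rounding). Opposite selection gives 22.3 − 16.7 = 5.6 points. Over the whole range, for one pair of branches (360 vs 420, alpha 0.05/10 = 0.005):

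| Selection | Spurious difference | Type I error |
|---|---|---|
| Response unrelated to outcome | 0 | 0.005 |
| Same in both (0.6 or 1.67) | 0.8 to 1.3 points | 0.007 to 0.008 |
| In one branch only (0.6 or 1.67) | 2.3 to 5.0 points | 0.021 to 0.082 |
| Opposite (0.6 control/text, 1.67 video) | 5.6 to 8.6 points | 0.20 to 0.35 |

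**5. A simple illustration.** Assume the first 60% of responders have a 25% rate and the extra 10% kept only in video branches have 10%: (0.6 × 0.25 + 0.1 × 0.10)/0.7 = 22.9%, a difference of −2.1 points. With 40% in the extra group it is +2.1. Taking a common rate of about 0.24:
- 720 vs 1,260 at 0.01: SE = √[0.24 × 0.76 × (1/720 + 1/1,260)] = 0.0200; 0.0214/0.0200 = 1.07; P(Z > 2.58 − 1.07) ≈ 6.7%.
- 360 vs 420 at 0.005: SE = √[0.24 × 0.76 × (1/360 + 1/420)] = 0.0307; 0.0214/0.0307 = 0.70; P(Z > 2.81 − 0.70) ≈ 1.8%.

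**The case against.** **A missing-data method may sit in an analysis plan that is not shown.** This is fair, and absence of a method alone would not be a point. What stands is that the protocol does set out its analyses, predicts a branch-caused imbalance on its main contrast, and names nothing that meets it.

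**Unequal dropout alone does not bias.** Correct. Response must also relate to outcome. The pilot's similarity on unprotected anal intercourse, which bears on one of the three primary outcomes, is evidence against strong selection. Adjustment for the pretest value and demographics also removes bias from dropout that those variables explain. Both points limit the likely size; neither removes the risk if the video itself changes who stays.

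**Stronger readings that the document does not support:**
- *That the protocol declares a completers-only analysis.* It does not. This is inferred from the paired test, the outcome definition and the power basis. The cleaning sentence concerns submitted surveys and does not say that cases are deleted.
- *That the intention-to-treat claim fails.* The statement promises that assignment is kept and follow-up sought; nothing contradicts that. It is incomplete.
- *That drug users in general drop out more.* The pilot gives a follow-up rate for methamphetamine users only.
- *That the pilot's fall in methamphetamine use from 7% to 5% demonstrates the bias here.* Dropout alone could move 7% to about 5.5%, so it may explain much of that fall. But it is a single-group change over time. McNemar's test on the same men avoids that artefact, and it says nothing directly about a between-branch difference.

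**Conclusion.** The point holds as a design weakness that should be corrected, not as a demonstrated error. As written, the primary comparison is in effect made among about 60% of men on one side and 70% on the other, with the gap attributed to the assigned condition. The comparison can be biased in either direction.

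The size cannot be read from the document; the figures above rest on assumed rates and odds ratios. If selection is mild and equal, the bias is about 1 point and type I error barely moves. It becomes material, roughly 2 to 9 points, only if selection differs between branches. That is plausible where a video is expected to hold men who would otherwise leave, but the document has no data on it.

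**What to change.** - State that the primary between-branch analysis includes all randomised men in their assigned branch.
- Handle missing 60-day outcomes by multiple imputation within branch, or by inverse-probability-of-response weights. Use the baseline outcome, drug and alcohol use, education, age and HIV status, plus post-intervention intentions where answered.
- Add a tipping-point analysis that varies the outcome rate among non-responders separately in branches 1–2 and branches 3–5, and report where the conclusion changes.
- Keep the responder analysis as a sensitivity analysis.
- Add differential attrition to the limitations, and reconcile the 1,980 implied by the branch rates with the 2,111 in the power section.

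No new data are needed: a completed baseline survey is an inclusion criterion, and intentions are sought from every branch. The cost is modest analyst time and possibly slightly wider intervals. Imputation and weighting still assume that the variables used explain response, which is why the tipping-point analysis belongs with them. The method should be fixed before follow-up outcomes are seen.

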**Incentives**

Research evaluating behavioral surveys administered over the internet has found that offering incentives likely increases the proportion of participants who enroll into a single study multiple times to maximize their ability to receive monetary reimbursement.48 In an effort to avoid or reduce the proportion of individuals who repeatedly enroll into this study, participants will not receive monetary reimbursement for completing study activities.

**Informed Consent Procedures**

The informed consent process for this study is in 2 parts: 1) Participants who click on a banner ad will be required to review and complete the online informed consent by clicking a button that indicates they read the consent form and wish to participate in the baseline survey. The consent form will state that the study is limited to persons aged 18 or older, for men who have sex with men, and addresses substance use and sexual risk behaviors associated with HIV transmission. Men who provide informed consent by clicking the consent form button will be allowed to enter the online baseline survey.

2) If the participant meets criteria for the intervention study (which will be automatically programmed to identify eligible participants), he will see another consent form that will invite him to participate in a brief intervention and ask for his email address. He will be informed that the study is randomized, and a brief description will be given for the study branches. If the participant consents by clicking the consent form button, then he will automatically be randomized into one of the assigned conditions. Before the participant begins the intervention, he will see information that clearly describes the assigned condition (i.e., prevention web page or video). For those who are assigned to the control condition, a screen will appear with the post-intervention questions, and then they will see a statement about being contacted in 60 days for a follow-up survey.

Intervention participants will be contacted via email 60 days post-intervention to complete the follow-up survey. A hyperlink will be embedded in the email, and when clicked on, will automatically transfer the participant to the consent reminder, which highlights the same information from the second consent. Men are given the opportunity to go on to the next page to begin the survey or to close their browser. Participants will be able to print copies of the consent forms and the reminder.

For participants who do not respond to the follow-up email, we will wait approximately 1 week before sending a first reminder email, approximately another week before sending the second reminder, and approximately one more week before sending the final reminder email (for an additional total of 21-30 days). The maximum number of days for completion of the follow-up survey will be 75 days.

**Justification to Waive Documentation of Consent**

Although Federal regulation requires that researchers obtain written informed consent for research on human subjects, under 45 CFR 46.117(c) written consent can be waived for research that involves minimal risk to participants and involves no procedures for which written consent is normally required outside of the research context.49 This research meets that criterion. We propose an alternative approach where participants click a button, signifying that they have read the informed consent page and agree to participate in the study. An advantage of Internet-based studies is that the consent form is available for the subject to review at any time.50 This strategy complies with the requirement of 46.117(c) that participants are given a written statement describing the research and risks.

